#### Blinding

The study uses a double-blind design, where both the patients and the study physicians will be blinded with regard to the group allocation of patients. The blinding process will be managed by the research assistant, who will administer medication/placebo and the novel tasting beverage. During the administration of medication and placebo, respectively, patients will be instructed to wear a sleep mask to prevent them from seeing the medication. Additionally, the width of the syringes will be standardised to 27-gauge for both the secukinumab and placebo injections, ensuring that patients will not be able to distinguish between the injected substances. Blinding will be implemented to prevent biased interpretations of objective symptom severity by the study physician and to avoid any negative treatment expectations caused by knowledge of the reduced medication dosage or placebo administration.

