#### Recruitment and enrolment of patients

Patients will be recruited from the outpatient department and from the inpatient wards of the Department of Dermatology, Venereology and Allergology at the University Hospital Essen, Germany. Recruitment will be conducted directly by the treating physician, who will inform patients with moderate-to-severe psoriasis about the option to participate in a study evaluating the influence of psychological factors on the effectiveness of systemic therapy with the IL-17 inhibitor secukinumab on subjective and objective outcomes. Additionally, informational flyers about the study for referring dermatologists will be included in the patients’ discharge letters.

Interested patients will be invited to a clinical visit (visit 0) at the study outpatient clinic, where they will be asked to provide written informed consent for participation by the treating study physician. Patients will be informed that they will be randomly assigned to one of three groups testing different dosing protocols for secukinumab, with some groups receiving lower doses than the standard regimen.

Additionally, patients will be informed that, depending on group assignment, they will receive a novel-tasting beverage alongside their injections at each visit. The patient information further includes a timeline indicating when psychological variables and biological samples will be collected. It will be emphasised that group allocation will be disclosed at the end of the study and that all patients will have access to standardised treatment with secukinumab or another therapeutic option after the study.

Patients will be fully informed about potential side effects, their right to withdraw their consent for the study at any time and the confidentiality of their data. On enrolment, each participant will be assigned a unique pseudonym through the ALIIAS software.^45^ The pseudonym will be linked to the web-based survey platform LimeSurvey,^46^ which will be used to collect the survey data for the study.

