#### Treatment phase and follow-up assessment

##### Visit 1

Similar to the procedure at visit 0, patients will start by completing psychological self-report questionnaires, followed by the clinical assessment conducted by the study physician. In contrast to visit 0, no biological samples will be collected. For patients assigned to one of the reinforcement groups, a 2-minute-35-second long medical educational video will be shown. The video will refer to a novel tasting green beverage, which, when taken in conjunction with the medication, can increase its effect via conditioning processes. Patients will be informed that they will receive the beverage immediately prior to their medication at every visit throughout the treatment phase. A literal transcription of the original German script as well as an English translation is provided as supplementary material (online supplemental text 1 and 2). The administration of the green beverage prior to the medication administration will be performed as the final step of each visit during the treatment phase.

##### Visit 2–visit 8

Procedures during visits 2 and 8 will be identical to those at visit 1, with the exception that additional blood samples will be collected during visits 5 and 8. An optional second skin biopsy will be collected prior to visit 7 to explore longitudinal changes in response to treatment.

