### Patient adherence and study discontinuation

To improve adherence to the intervention protocol, all medication or placebo injections will be administered by the research assistant at the clinical study centre, which requires the attendance of patients. Similarly, all questionnaire data will be assessed prior to the medication administration on site.

Given the relatively low dosages of secukinumab in the reinforcement groups, topical treatments will be permitted as concomitant care in all three groups to enhance adherence and reflect real-life clinical care, as recommended by the S3 guideline for the treatment of psoriasis vulgaris. The study participation will be discontinued at any time at the patient’s request, if side effects are deemed intolerable by the patient and/or the treating physician or if the patient misses more than one visit. In such cases, the patient will be unblinded to the treatment allocation to allow appropriate subsequent medical care.

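### The trial is labelled double-blind, but the drink and video mark out the reinforcement arms, so patients are not blinded in the TAU-versus-reinforcement comparison of hypotheses 1 and 3

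*Protocol article*

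**What the plan says.** The Blinding section of the protocol article states: "The study uses a double-blind design, where both the patients and the study physicians will be blinded", and the sentence goes on to say that this covers group allocation. It gives two reasons: to keep the physician's severity rating unbiased, and "to avoid any negative treatment expectations caused by knowledge of the reduced medication dosage or placebo administration". On the patient side it describes a mask over the eyes ("patients will be instructed to wear a sleep mask to prevent them from seeing the medication") and the same 27-gauge width for every injection.

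Under Trial design, Dosing schedule and administration, and Visit 1, the drink and the video are assigned to the two reinforcement groups only. The video presents the drink as something that, taken with the medication, "can increase its effect via conditioning processes". No sham drink or neutral video is described for TAU.

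Under Recruitment and enrolment of patients, all patients learn that they will be randomised to one of three dosing protocols, "with some groups receiving lower doses than the standard regimen", and that "depending on group assignment, they will receive a novel-tasting beverage alongside their injections at each visit". They are also told that allocation will be revealed when the study ends.

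**The concern.** A patient who drinks a green lavender-flavoured milk before each injection knows which side of the TAU-versus-reinforcement divide they are on, and so does a patient who never gets one. Masking the syringe cannot undo that. Hypothesis 1, the non-inferiority test, and hypothesis 3, on side effects, both compare TAU with the pooled reinforcement groups. Two of the three hypothesis 1 outcomes (itch and DLQI) are rated by the patient, as is GASE in hypothesis 3. The Introduction itself describes itch as strongly open to psychological influence.

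At stake is whether the results on these outcomes can be reported as coming from a patient-blinded comparison. As the design is described, they cannot. The limitations listed at the front of the article mention the missing low-dose, non-conditioned control but not this.

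**Working it through.** The claim is checked by setting sections side by side; the document states no figure for it that could be reproduced.

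**1. What each measure hides.**

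| Feature | TAU | Partial | Continuous | Reveals TAU versus reinforcement to the patient? |
|---|---|---|---|---|
| Injection, sleep mask, 27-gauge | yes | yes | yes | no |
| Drink at treatment visits | none described | yes | yes | yes |
| Video at visit 1 | none described | yes | yes | yes |
| Attribution item on the drink (visits 2 and 9) | no | yes | yes | yes |

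The last three rows separate TAU from reinforcement completely and do not separate partial from continuous. Blinding can therefore hold for hypothesis 4 and cannot hold for the TAU contrast.

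**2. How closely the drink tracks dose.** TAU has 5 weekly and 3 monthly injections of 300 mg: 8 × 300 = 2400 mg. Continuous reinforcement has 2 × 300 + 6 × 75 = 1050 mg. Partial reinforcement, if the alternation runs through the monthly visits, has 2 × 300 + 3 × 150 = 1050 mg, which agrees with the statement that both groups receive the same total. Every drink patient is on the reduced total and no TAU patient is.

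**3. Who is affected.** The planned sample is 168 with 84 in TAU, leaving 168 − 84 = 84 in the pooled reinforcement groups. All are on one side or the other of the visible split.

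**4. Which ratings are affected.** At visit 1 the questionnaires come first and the video and drink come later. Visit 1 ratings thus precede the cue, and those from visits 2 to 9 follow it:

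- itch (visits 1–9): 9 − 1 = 8 of 9 ratings
- DLQI (visits 0–9): 10 − 2 = 8 of 10
- GASE (visits 1–9): 9 − 1 = 8 of 9

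The pre-measurement is taken before patients know and the post-measurement after, so any effect of knowing enters the change score directly.

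**5. Direction.** Suspecting a lower dose could worsen ratings in the reinforcement arms, and being told that the drink strengthens the drug could improve them. TAU patients may also react to receiving no drink. The document gives no basis for netting these out.

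**6. PASI.** The physician has no access to the randomisation list, the research assistant gives the injections and the drink, and the drink comes last at each visit. The remaining route is a patient mentioning the drink at a later visit.

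**The case against.** **Consent does not link drink to dose.** This stands. The two facts are disclosed separately, and nothing shown tells patients whether a full-dose group also gets the drink. A reader might conclude that patients are told they are on a reduced dose; the text does not support that. Drink or no drink is certain knowledge, and dose is an easy inference. The certain part alone is enough to contradict blinding to group allocation.

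**The expectation effect is part of the treatment.** This largely stands. Drink plus information is the package under test, so a response to the video's message is not simply bias, and a matched drink in TAU need not be demanded. It does not make the statement about patient blinding true, and it does not cover reactions to a suspected lower dose or to getting no drink.

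**Expectations are already measured.** In part. Expected DLQI and expected severity (visits 1, 5, 7 and 9), perception of the drink (visits 5, 7 and 9) and attribution (visits 2 and 9) are collected. None of these items, as described, asks which group or dose patients believe they have.

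**An article condenses the full protocol.** That would excuse an omission. Here the text makes a positive claim that its own description of the interventions contradicts.

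**Topical treatment.** The article says: "Given the relatively low dosages of secukinumab in the reinforcement groups, topical treatments will be permitted as concomitant care in all three groups". A reader might infer that unblinded patients will use more topicals and so shift hypothesis 1 towards non-inferiority by some number of points. The document gives neither a difference in use nor an effect of use. Greater use could also follow from weaker disease control under perfect blinding, and recording and analysis of topicals may sit in the full protocol. No estimate is made, and the point does not rest on it.

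**Conclusion.** The label is wrong as written for the comparison that carries hypotheses 1 and 3. As described, the design blinds patients to injection content and can blind them to partial versus continuous reinforcement, but not to TAU versus reinforcement. Self-rated itch, DLQI and GASE are open to bias in that contrast for all 84 versus 84 planned patients and at every rating from visit 2 on. Neither the size nor the net direction of the bias can be derived from the document, so it should not be read as a bias known to favour non-inferiority.

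This rests on two assumptions: TAU patients receive no matching drink or video, since none is described, and visit procedures run in the order given. It does not assume that every patient works out their dose. Nor does it follow that PASI must become a gatekeeper for any non-inferiority conclusion. That would change the confirmatory structure, in which the Outcomes section places PASI among the secondary outcomes and hypothesis 2 expects slower PASI improvement in the experimental groups.

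**What to change.** 1. Replace the double-blind statement with: *PASI-rating physician blinded; patients blinded to injection content and to partial versus continuous reinforcement, but not to TAU versus reinforcement.*
2. Add one item at late visits, visit 9 among them, asking patients and the physician which group and dose they believe the patient received, and report the answers by arm. Late guesses also reflect how well the patient has done, so the result is descriptive and should not be used as an adjustment variable.
3. Instruct patients not to mention the drink to the physician.
4. State as a limitation that conclusions on self-rated outcomes under hypotheses 1 and 3 do not come from a patient-blinded comparison and should be read alongside the blinded-rater PASI.

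Recruitment is planned until 30 June 2027, so an amendment can still benefit patients yet to be enrolled. The cost is some wording, a short questionnaire addition and one instruction. The downsides are a slightly longer visit and a weaker blinding claim.

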### Patient and public involvement statement

Patients and the public were not involved in the development of the research questions, outcome measures, study design, recruitment or conduct of the study. Further, patients were not involved in assessing the burden of the intervention or the time required to participate in the study. However, a patient advisory board was consulted prior to the start of the study to evaluate the medical educational video used within the intervention. Dissemination of the study results to healthcare professionals and the general public will be conducted as part of the overarching communication strategy of the CRC 289 ‘Treatment Expectation’.

### Ethics and dissemination statement

The study protocol was approved by the ethics committee of the University Hospital Essen (19–8636 BO) on 20 November 2023. Written informed consent will be obtained from all participants. Participant confidentiality will be ensured through pseudonymised data handling and secure storage. The results will be disseminated through peer-reviewed publications.

### Data management

All study data will be collected electronically during on-site visits using tablet devices. Standardised psychometric questionnaires were programmed and will be implemented via the platform LimeSurvey.^46^ Data collected via LimeSurvey will be automatically pseudonymised using the ALIIAS software.^45^ These pseudonymised data will be transferred to the AutoCRF infrastructure, which performs automated checks for completeness and plausibility. Raw and processed data will be securely stored in the project-specific directories within the centralised infrastructure of the collaborative research centre. Only authorised study personnel will have access to these data.

Printed and electronic versions of patient consent forms and contact information will be stored separately at the outpatient clinic, with access restricted to authorised personnel only.

### Analysis plan

All statistical analyses will be conducted using R^64^ (V.4.1.1.; R Core Team, Vienna, Austria) within RStudio^65^ (RStudio Team, Boston, MA).

Confirmatory hypotheses will be tested using linear mixed models, assuming approximate normality of random effects and residuals. If model diagnostics indicate substantial violations of distributional assumptions, generalised linear mixed models with appropriate link functions and distribution will be applied based on the observed characteristics of the data.

Each model will include Group as a between-subject factor and Time (10 levels, one per visit) as a within-subject factor. The Group factor represents the treatment conditions (TAU, partial reinforcement and continuous reinforcement). The number of Group levels varies by hypothesis and will be specified within each hypothesis section. Random intercepts for participants will be included to account for individual differences. Random slopes will be added if they significantly improve model fit, as evaluated by likelihood ratio tests and information criteria (ie, Akaike Information Criterion, Bayesian Information Criterion).

Main effects and Group × Time interactions will be examined depending on the respective hypotheses. Pairwise comparisons of estimated marginal means will be conducted where appropriate, with Holm-adjusted p values used to control for multiple comparisons, particularly given the unbalanced group sizes. A significance level of α=0.05 will be applied for all confirmatory tests.

#### Hypothesis 1

We hypothesise that both experimental treatments (pooled across partial and continuous reinforcement) will be non-inferior to the TAU group regarding average reductions in itch, PASI and DLQI scores from pre-measurement to post-measurement. Non-inferiority testing will be embedded within the linear mixed model framework. One-sided 95% CIs will be computed based on model estimates. Non-inferiority will be concluded if the upper bound of the CI lies below the predefined MCID of 25%.^66^

#### Hypothesis 2

We hypothesise that symptom trajectories differ between groups. Specifically, both experimental groups are expected to show slower improvements in objective disease severity (ie, PASI scores), while improvements in subjective symptoms (ie, itch and DLQI scores) are expected to be comparable to those in the TAU group. Group × Time interactions will be modelled to identify differential symptom trajectories. Given the absence of prior data on the exact shape of these trajectories, no assumptions about their functional form are made beyond the directionality stated above. Post hoc contrasts will be conducted to explore group differences at specific time points or in change patterns across the study period.

#### Hypothesis 3

As part of hypothesis 3, we examined potential effects on secondary outcomes, namely side effects. Specifically, we hypothesise that participants in the experimental groups (pooled across partial and continuous reinforcement) will report fewer side effects from pre to post compared with the TAU group. A linear mixed model with a Group × Time interaction will be fitted to side effect scores derived from the GASE questionnaire.

#### Hypothesis 4

Supplementary to the other hypotheses, a subsequent analysis focusing on the two reinforcement groups will examine potential differences in both overall and longitudinal effects of the various dosing regimens. We hypothesise that the partial reinforcement group will show stronger treatment effects on outcomes compared with the continuous reinforcement group. Specifically, we expect significantly greater average reductions in itch, PASI and DLQI scores over time. This hypothesis will be tested via the Group × Time interaction across all 10 measurement points. If the interaction is significant, follow-up contrasts will compare the estimated change trajectories between the two experimental groups, with a focus on overall pre–post improvement and the rate of change over time.

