### Outcomes

#### Primary outcomes

##### Itch

The change in itch severity will be assessed as primary outcome throughout the intervention and follow-up phase. Participants will be asked to rate the most severe itch as well as the average itch experienced over the last 24 hours on a Visual Analogue Scale (VAS). The scale ranges from 0 (‘no itch’) to 100 (‘most severe itch imaginable’). Specifically, participants will be asked: ‘How severe was the most intense itch you experienced in the last 24 hours?’ (German: ‘Wie stark war der schlimmste Juckreiz, den Sie in den letzten 24h gespürt haben?’) and ‘How severe was your average itch in the last 24 hours?’ (German: ‘Wie stark war Ihr durchschnittlicher Juckreiz in den letzten 24h?’). This measurement will be carried out during visits 1–9.

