#### Group allocation

The allocation of patients to the study groups will take place after enrolment and receipt of written informed consent. To balance disease severity between groups, the randomisation of patients will follow a stratified randomisation schedule based on PASI scores and will be carried out by the research assistant. The stratified randomisation schedule will be generated prior to study initiation by a postdoctoral researcher who is not involved in patient care, recruitment or data collection. The study physician will have no access to the randomisation list. Prior to recruitment, two strata were established based on PASI scores: 60% of patients were expected to have a PASI ≤15 and 40% a PASI of >15. Within each stratum, randomisation to one of the three intervention groups will be performed using computer-generated random numbers. These numbers will be generated using an Excel spreadsheet and will determine the respective group assignments. To ensure blinding, the group assignment will be initially blackened out, with the group only revealed after the assignment has been completed.

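### The mixed model lets the groups differ at visits measured before any dose, which widens the pre-post non-inferiority interval, and its ten time levels do not exist for itch or side effects

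*Protocol article*

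**What the plan says.** All places are in the Protocol article.

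- **Model (Analysis plan).** "Each model will include Group as a between-subject factor and Time (10 levels, one per visit) as a within-subject factor". "Random intercepts for participants will be included to account for individual differences", with random slopes only if they improve fit. "Main effects and Group × Time interactions will be examined depending on the respective hypotheses". Neither a baseline term nor a stratum term is named.
- **Contrast (Hypothesis 1).** Pooled reinforcement is compared with treatment-as-usual "regarding average reductions in itch, PASI and DLQI scores from pre-measurement to post-measurement". The decision rests on the upper limit of a one-sided 95% interval against a 25% margin.
- **Randomisation (Group allocation).** "the randomisation of patients will follow a stratified randomisation schedule based on PASI scores", in two strata: "60% of patients were expected to have a PASI ≤15 and 40% a PASI of >15".
- **Pre-dose visits.** Visit 0 precedes treatment (Baseline assessment). At visit 1 the questionnaires and the clinical assessment come first; the video, drink and injection follow (Visit 1; Patient adherence and study discontinuation).
- **Measurement times.** For itch: "This measurement will be carried out during visits 1–9". The GASE section also gives nine time points, visits 1 to 9. DLQI and PASI are taken at every visit, which makes ten. Hypothesis 4 nevertheless repeats the count of ten for itch, PASI and DLQI together.

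**The concern.** A group difference observed at visit 0 or 1 can only be chance, because no patient has yet had a dose, the drink or the video. A model with a free group-by-visit mean at those visits subtracts that chance difference in full from the difference at the end. Holding the groups equal before dosing, or adjusting for the baseline value, subtracts only the part that predicts the later value. Non-inferiority is decided on a confidence limit, so unnecessary width directly lowers the chance of showing it.

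The time factor raises a second problem. A ten-level factor cannot be fitted to an outcome measured nine times. The mismatch also draws attention to an undefined term: 'pre' can only be visit 1 for itch, but for PASI and DLQI it could be visit 0, visit 1 or both.

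**Working it through.** **Inputs.** The protocol gives no SD, standard error or correlation for these outcomes, so there is no figure of its own to reproduce. To set a scale I take 76 patients per side (152/2, from Sample size) and a total SD of 1. The ratios below depend on neither. The within-patient correlation rho is an assumption, shown from 0.3 to 0.8. The covariance is that of the stated random-intercept model (equal variances, equal correlations), and 'post' is a single visit.

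**One pre-dose visit (itch, GASE).** With n per side:

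- As stated: SE² = (2/n) × 2(1 − rho)
- Equal pre-dose means: SE² = (2/n) × (1 − rho²)
- Ratio of interval widths: √[2/(1 + rho)]

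At rho = 0.5: √(0.02632 × 1) = 0.162 against √(0.02632 × 0.75) = 0.141.

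**Two pre-dose visits (PASI, DLQI).**

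- As stated, 'pre' = visit 0: SE² = (2/n) × 2(1 − rho)
- As stated, 'pre' = mean of visits 0 and 1: SE² = (2/n) × 1.5(1 − rho)
- Equal pre-dose means at both visits: SE² = (2/n) × (1 − rho)(1 + 2rho)/(1 + rho)
- Ratios of widths: √[2(1 + rho)/(1 + 2rho)] from visit 0, and √[1.5(1 + rho)/(1 + 2rho)] from the mean

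| rho (assumed) | Itch: SE stated / constrained | Itch: extra width | PASI, DLQI from visit 0: extra width | PASI, DLQI from mean of 0 and 1: extra width |
|---|---|---|---|---|
| 0.3 | 0.192 / 0.155 | 24% | 27% | 10% |
| 0.5 | 0.162 / 0.141 | 15% | 22% | 6% |
| 0.7 | 0.126 / 0.116 | 8.5% | 19% | 3% |
| 0.8 | 0.103 / 0.097 | 5% | 18% | 2% |

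Simulated REML fits of the itch model (60 runs per setting) gave mean SEs of 0.191 against 0.154, 0.162 against 0.141, and 0.126 against 0.116 at rho 0.3, 0.5 and 0.7. They agree with the formulas.

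For itch the variance ratio is 2/(1 + rho), which runs from 1.11 at rho 0.8 to 1.54 at rho 0.3. The stated contrast would therefore need about 11–54% more patients for the same precision.

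**The stratum.** A stratum main effect adds the same constant to a patient's pre and post values, so it cancels from the change. At rho 0.5 the unconstrained SE is 0.162 with or without it. It can matter in two ways:

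- *Alongside the baseline constraint*, it narrows the SE a little further, by up to about 7% at rho 0.3 under the strongest stratum effect tried (0.155 to 0.144).
- *With its Time interaction*, in a PASI-like simulation with assumed proportional improvement, the mean model SE fell from 0.659 to 0.583. The baseline constraint alone gave 0.549, and both together gave 0.484.

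**Time levels.** Visits 0 to 9 make ten; visits 1 to 9 make nine. The count of ten holds for PASI and DLQI and fails for itch and GASE. The imputation rule in Missing data handling (at least 7 of 10 time points, at most 30% missing) inherits the error. For itch, seven observed visits out of nine possible means 2/9 = 22% missing.

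**The case against.** The strongest reply is that this is a condensed article. Stratification factors and baseline covariates are commonly left to the analysis plan, and saying that a model will include Group and Time does not exclude other terms. That stands as far as silence goes: the mere absence of a covariate would not be a finding. But the article does fix something, namely one Time level per visit for every model. That places the pre-dose visits on the outcome side, with Group × Time and no stated restriction. It also states a count that its own measurement schedule contradicts.

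Two further replies stand in full. The stated model is a standard and valid longitudinal model. And the size of the loss cannot be fixed from the protocol: at high correlation, or with the mean of both pre-dose visits as 'pre', it is small.

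Three stronger readings are tempting, and the document does not support them:

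- *Leaving out the PASI stratum is what widens the interval.* It is not, because a stratum main effect cancels from a pre-post contrast.
- *Baseline adjustment would cut the variance to about a third.* That needs, for example, a post SD of 0.6 of baseline with rho 0.3: 0.36 × 0.91 / (1 + 0.36 − 0.36) = 0.33. The stated random-intercept model has equal variances, and the protocol gives no SDs to support the figure.
- *The non-inferiority test is biased, or its power is below target.* Neither follows. The contrast is unbiased, and without an SD the power of the mixed-model test cannot be computed.

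On the time levels, software would simply fit nine for itch, so no itch estimate changes. The passages still disagree, and 'pre' for PASI and DLQI remains open.

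**Conclusion.** The point holds as a loss of precision and an internal contradiction. Leaving the groups free before dosing makes the interval 5–24% wider for itch. For PASI and DLQI the figure is 18–27% or 2–10%, depending on which pre-dose visit or visits count as 'pre'. These figures assume rho between 0.8 and 0.3, the equal-variance random-intercept structure, and a single post visit. The direction holds for any rho from 0 to below 1. Non-inferiority becomes harder to show, and type I error is not inflated.

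The missing PASI stratum is secondary: it affects this contrast only through its Time interaction or together with the baseline constraint. The conflict between ten levels and nine visits is certain and needs no assumption.

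The change should be made, because it gains precision from data already being collected and because the choice of baseline is open to challenge if made after unblinding.

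**What to change.** In the Analysis plan:

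1. Constrain the group means to be equal at the pre-dose visits (0 and 1 for PASI and DLQI; 1 for itch and GASE). Alternatively, use the baseline value as a covariate with its visit interaction and keep only post-dose visits as outcomes.
2. Include the PASI stratum with its Time interaction, or alongside the baseline constraint. A main effect by itself is not enough.
3. State nine Time levels with visit 1 as baseline for itch and GASE, and ten levels for PASI and DLQI.
4. State which pre-dose visit or visits define 'pre' for PASI and DLQI.
5. Correct the count of ten in Hypothesis 4, and the 7-of-10 imputation rule, for outcomes measured nine times.

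The cost is wording only. All the values are already collected, and neither the sample size nor the visit schedule changes. It should be settled before unblinding.
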